# The value of INnovative ICT guided disease management combined with Telemonitoring in OUtpatient clinics for Chronic Heart failure patients. Design and methodology of the IN TOUCH study: a multicenter randomised trial

**DOI:** 10.1186/1472-6963-11-167

**Published:** 2011-07-13

## Abstract

**Background:**

Although the value of telemonitoring in heart failure patients is increasingly studied, little is known about the value of the separate components of telehealth: ICT guided disease management and telemonitoring. The aim of this study is to investigate the value of telemonitoring added to ICT guided disease management (DM) on the quality and efficiency of care in patients with chronic heart failure (CHF) after a hospitalisation.

**Methods/Design:**

The study is divided in two arms; a control arm (DM) and an intervention arm (DM+TM) in 10 hospitals in the Netherlands. In total 220 patients will be included after worsening of CHF (DM: N = 90, DM+TM: N = 130). Total follow-up will be 9 months. Data will be collected at inclusion and then after 2 weeks, 4.5 and 9 months. The primary endpoint of this study is a composite score of: 1: death from any cause during the follow-up of the study, 2: first readmission for HF and 3: change in quality of life compared to baseline, assessed by the Minnesota Living with Heart failure Questionnaire. The study has started in December 2009 and results are expected in 2012.

**Conclusions:**

The IN TOUCH study is the first to investigate the effect of telemonitoring on top of ICT guided DM on the quality and efficiency of care in patients with worsening HF and will use a composite score as its primary endpoint.

**Trial registration:**

Netherlands Trial Register (NTR): NTR1898

## Background

Heart failure (HF) is the most common hospital discharge diagnosis in elderly patients [1]. Between the age of 70 and 80 years the incidence of HF is 10 to 20%. HF is associated with high mortality and morbidity, readmission rates and costs [1]. The readmission rates vary between 25% and 50% within 6 months after the first hospitalisation for HF, with a higher readmission rate within the first month after discharge[2,3]. The costs related to HF contribute to 1-2% of all healthcare expenditures and are mainly the result of hospital stay [4-6]. Because of an increasing shortage of resources, HF is a major public health problem and therefore, a more effective and efficient organisation of care for HF patients needs to be reconsidered. A first step in organising treatment and care for patients with chronic HF more efficiently, was the implementation of specialised outpatient HF clinics. In the recent European Society of Cardiology (ESC) guidelines, HF management programmes are strongly recommended for all patients with HF [1] and HF clinics are considered as 'usual care' in several European countries [7]. A widely used way to implement HF management is the use of specific disease management (DM) programs.

DM can be defined as an intervention, designed to manage a chronic disease and to reduce hospital readmissions, using a systematic approach to care and potentially employing multiple treatment modalities [8]. Control and cost effectiveness are substantial components of a DM program. Randomised studies suggest that DM programs can reduce readmissions for HF or cardiovascular disease with 30% [7,9,10] and significantly decrease mortality rates [11]. Yu et al [12] described that DM for HF patients, as recommended by the ESC guidelines, [1] are effective in reducing hospital readmissions and mortality rate [13]. However, inconsistent findings for readmission and mortality rates have been found, probably due to the variety of components and practical applications of the DM programs.

We recently reported results of the COACH study, a study on the effect of a nurse led DM program on clinical outcome [14], in which the positive effects of a DM program on readmission were not confirmed, although there was a trend to a reduction of mortality in the intervention groups. The INH study [15] on the effect of DM in HF, showed that a DM program compared to usual care could reduce mortality but not hospitalisation rates. Important components of this program were patient education, optimisation of medical therapy, psychosocial support and an easy access to healthcare. An important aspect for the treatment of HF patients is the prescription of HF related medication at an optimal dose i.e. ACE-inhibitors, beta-blockers, and aldosteronantagonists. The up titration to optimal dosage is an aspect that often takes place at a HF outpatient clinic. However, data from the Euro Heart Failure Survey showed us that guideline adherence for HF medication although improving still is not optimal[16]. In the IMPROVE study, dedicated HF clinics were associated with greater use of cardiac resynchronisation therapy and a better HF education, but not with better guideline adherence to medication [17]. Health information technology, integrated into a DM program might facilitate adherence to guidelines of health professionals [18]. With new information and communication technology (ICT), healthcare providers can be supported in the diagnosis, treatment and follow up of HF patients by expert computerised systems, based on guidelines and protocols [19]. These systems can be used to optimise medication according to guidelines and provide structural support and education [20]. We were the first to report promising findings on ICT guided DM in terms of higher doses of recommended HF medication and lower readmissions [21,22]. Another promising ICT tool is telemonitoring. Telemonitoring is often used to monitor patients at home and guide patients to take action in case of deterioration, but it also can be used to up-titrate medication according to guidelines at distance [23]. There is support that remote monitoring of patients with HF can reduce hospitalisation and mortality rates, [24,25] however results on clinical outcome and efficacy are inconclusive and limited [26-28]. There are also recent study's that where not successful in their primary endpoints [29,30]. Furthermore, cost-effectiveness of these systems has not been thoroughly evaluated. It can be concluded that the overall effects of telemonitoring are inconclusive. To summarise, due to a growing population of patients with HF and an expected shortage of healthcare providers in the near future, there is a need to seek to more cost effective and efficient ways of providing optimal care for HF patients, including a better adherence to guidelines. ICT guided DM tools in combination with telemonitoring could be of important value [31,32]. At the same time there is substantional data that the adaptation and implementation of those systems is lacking [33]. The experiences with such a system however are fragmented. User resistance is described as a major obstacle in the adoption of these computerised tools. More insight in user resistance and experienced barriers in using ICT guided DM tools is needed to successfully implementing such tools [34].

The IN TOUCH study will investigate the effect of telemonitoring in addition to an ICT guided DM system on the quality and efficiency of care for patients after worsening HF. This is the first study investigating a combination of two newly developed ICT interventions in a group of chronic HF patients on clinical outcome, adherence to guidelines, cost effectiveness and quality of life.

This study will add important information to other telemonitoring studies because of its strong commitment to ICT guided DM, the chosen composite endpoint, a strong focus on cost-effectiveness and the investigation of the influence of user aspects as resistance and barriers that accompany the use of modern healthcare related ICT tools.

## Methods/Design

### Study hypothesis

Telemonitoring added to ICT guided DM improves prognosis and quality of life in patients with HF compared to ICT guided DM alone.

### Aim of the study

The primary aim of this study is to assess the effect of telemonitoring on top of an ICT guided DM system in patients after worsening HF on the combined endpoint of death, readmission and quality of life, compared to patients treaded with ICT guided DM alone.

Secondary aims of the study are;

• To assess the effect of telemonitoring in addition to an ICT guided DM system compared to an ICT guided DM alone on the separate components of the combined endpoint (death, readmission and quality of life).

• To determine the cost benefit ratio of ICT guided DM with telemonitoring compared to ICT guided DM alone.

### Study design

A multicentre, randomised study in which in total 220 HF patients (NYHA II-IV) will be included. Patients will be randomised to the ICT guided DM (control) arm (N = 90) or into the ICT guided DM with telemonitoring (intervention) arm (N = 130) (Figure 1).

**Figure 1 F1:**
[figure not shown]
Flowchart of the inclusion.

### Study population

All patients admitted to the intensive care/coronary care unit or cardiology ward for HF or visiting the outpatient clinic with worsening HF who need treatment or adjustment of oral or intravenous diuretics, can be included in the study. Other inclusion criteria are; evidence of structural underlying heart disease, left ventricular ejection fraction ≤ 45% and age of at least 18 years. Reasons for exclusion are myocardial infarction in the past month, cardiac invasive intervention (percutaneous coronary intervention, coronary arterial bypass, valve replacement, heart transplantation, or cardiac resynchronisation therapy) in the past 6 months or planned in the next 3 months, weight > 200 kg, actual haemodialysis and the use of other telemonitoring systems (Table 1).

**Table 1 T1:** In and exclusion criteria IN TOUCH

***Inclusion criteria***
Worsening HF defined as signs of fluid retention (peripheral oedema/congestion) needing an increase of the dose of diuretics (i.v. or oral)
Evidence for structural underlying heart disease
Documented reduced left ventricular ejection fraction (LVEF) ≤45%
18 years of age
Patients have to be able to understand content of and willing to provide informed consent.
***Exclusion criteria***
History of myocardial infarction in the previous month
Life expectation less than 1 year
Undergone cardiac invasive intervention within the last 6 months (PCI, CABG, HTX, valve replacement, CRT implantation)
A planned procedure for PCI, CABG, HTX, CRT implantation or valve replacement in the following 3 months
Evaluation for heart transplantation prior to or during the study
Weight more than 200 kilogram
The use of telemonitoring devices at home
Haemodialysis

### Primary endpoint

The primary endpoint of the study is a composite, weighted score consisting of values for mortality, HF readmission and change in quality of life between end of the study and baseline measured with the Minnesota Living with HF Questionnaire (MLHFQ), adapted from the A-HeFT study [35] (Table 2). A readmission for HF is defined as an overnight hospital stay for HF or directly related to HF. The readmissions for HF will be blinded adjudicated by an endpoint committee. When data on quality of life are missing, the worst-case score for that component of the composite endpoint will be used in the analysis.

**Table 2 T2:** score system for primary endpoint IN TOUCH

End point	Score
Death (at any time during study)	-3
Survival to end of study	0
First readmission for heart failure	-1
No readmission for heart failure	0
	
*Change in quality of life at 9 months*	
Improvement ≥ 20 units	+2
Improvement by 10 until 19 units	+1
No improvement by -9 until +4 units	0
Worsening by +5 until +9 units	-1
Worsening by ≥ 10 units	-2
	
*Possible score*	-6 to +2

### Secondary endpoints

Secondary endpoints of the study are the separate components of the primary endpoint. Other secondary endpoints are the total number and duration of all hospital admissions, treatment according to the guidelines using the criteria of the Guidelines Adherence Indicator-3 [36], number of visits to the outpatient HF clinic, patient and carer satisfaction, and cost-benefit ratio.

### Ethics statement

On March 2009 this study design has became ethical approval (M09.070323) given by the medical ethical commission (MEC) of the medical university of Groningen (UMCG).

The study has started (first patient) in December 2009.

### Incremental cost-effectiveness ratio (ICER)

Costs A distinction will be made between intervention costs and resource utilization costs. The intervention costs consist of the costs of the DM system and the costs of the telemonitoring devices and will be calculated as a lump-sum over the study's follow-up period. Resource utilisation costs will be estimated by preparing a structured data collection form to collect detailed information regarding scheduled and non-scheduled outpatient clinic visits and hospital admissions (both HF and non-HF related), ward type (e.g. intensive/coronary care unit, cardiology, general internal medicine), and cardiovascular procedures/operations. In addition, a patient questionnaire will be administered at 4.5 months and 9 months of follow-up to collect complementary data on general practitioner visits, home care utilization, and nursing home admissions. Unit costs will be estimated by using the Dutch guidelines for cost calculations and inflated to current price levels using a general consumer price index. Indirect costs, such as productivity losses, will not be taken into account.

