### Randomisation and data collection

Patients can be randomised during admission for HF, and in case of worsening of HF at the outpatient clinic. After confirmation of eligibility and written informed consent, patients will be included into the study. Patients will be randomised into the control or intervention group. Patient characteristics and clinical variables will be collected at baseline, and 2 weeks and 9 months after discharge. Echocardiography, ECG, and laboratory analysis will be performed at baseline during hospitalisation and at the end of the study. Quality of life as part of the primary endpoint, measured with the Minnesota Living with HF Questionnaire, will be collected at baseline and at 9 months. Data about utilisation of resources will be collected prospectively and comprise components of direct costs, i.e. scheduled and non-scheduled outpatient visits and hospital admissions.

Questionnaires about self-care behaviour, anxiety, depression, compliance and medical technology assessment (MTA) will be completed before discharge, and at 4.5 and 9 months (Table 3). Patients should be included preferably as soon as possible but at least within a period of time of 14 days after discharge or after the first visit at the HF clinic with worsening HF.

**Table 3 T3:** Questionnaires and medical assessment used in the IN TOUCH

*Questionnaires *	Baseline	2 weeks	4,5 month	9 month
Minnesota Living with Heart failure Questionnaire (MLHFQ)	•			•
Revised Heart failure Compliance	•			•
Disability Rating Index (VAS)	•			•
Hospital Anxiety and Depression scale (HADS)	•			•
Heart failure self-care behaviour scale (EHFScB)	•			•
Medical technology assessment (MTA)			•	•
EQ-5D	•		•	•
Satisfaction questionnaire for patients and providers				•

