### Intervention group

#### ICT guided disease management with telemonitoring

Patients in the DM with telemonitoring group will be treated with the above described ICT guided DM system in combination with the following integrated telemonitoring devices that will be installed at the patients' home;

• weighing scale; patients will be instructed to weigh daily.

• blood pressure meter; patients will be instructed to measure their blood pressure daily during up titration of medication.

• ECG; patients have to perform an ECG twice a week during up titration of beta-blockers.

• Health monitor; an interactive monitor collects data from the weighing scale, blood pressure meter and ECG device and will respond to the patients' collected data. Data will be directly transmitted to the DM system in the hospital.

In case of a deviation of individualised predefined ranges of weight, blood pressure or heart rhythm, the health monitor will automatically generate supplementary questions directly to the patient to evaluate the actual health situation. This data, measurements and subjective patient information (predefined multiple choice questions about HF symptoms) will be transferred to the computerised DM in the hospital. Furthermore, the health monitor will generate an advice about the non-pharmacological treatment, for example regarding compliance with fluid and sodium restriction. When the data collected by the system deviates from predefined ranges, the HF nurse will be informed automatically by mobile phone and email. In that case, the HF nurse will contact the patient by phone within two hours and further discusses symptoms and treatment. If data are outside any reference range in combination with symptoms of deterioration, patients will receive a message from the health monitor that they will be contacted by the HF nurse.

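### The listed costs leave out HF-nurse time for handling telemonitoring alerts, which arises only in the DM+TM arm, so incremental cost is understated if the list is followed as written

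*Protocol article*

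**What the plan says.** The section on the incremental cost-effectiveness ratio divides costs into two groups. The first is defined thus: "The intervention costs consist of the costs of the DM system and the costs of the telemonitoring devices". These are entered as one lump sum for the whole follow-up. For the second, resource use, a structured form is to collect "detailed information regarding scheduled and non-scheduled outpatient clinic visits and hospital admissions (both HF and non-HF related), ward type" and cardiovascular procedures. A patient questionnaire at 4.5 and 9 months adds "complementary data on general practitioner visits, home care utilization, and nursing home admissions". Unit costs follow the Dutch costing guidelines. The only declared exclusion is indirect cost such as lost productivity.

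The section on the intervention group describes what follows an out-of-range measurement: "the HF nurse will be informed automatically by mobile phone and email". The next sentence sets out the nurse's task: "In that case, the HF nurse will contact the patient by phone within two hours and further discusses symptoms and treatment". The control group uses the same disease management system without telemonitoring and so has no alert pathway.

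The costs feed the incremental cost per QALY and the acceptability curves in the Cost-effectiveness section. The cost-benefit comparison is a secondary aim and a secondary endpoint.

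**The concern.** The nurse's response to an alert is part of how telemonitoring is meant to work, and it is paid staff time. It is a direct care cost, so the exclusion of indirect costs does not cover it. No item in either cost group names telephone contacts, alert review or nurse time. The device is therefore charged to the DM+TM arm, but the work it triggers is not.

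At stake is the economic comparison. The article motivates the trial partly by an expected shortage of healthcare providers and by the hope of lower workload. An evaluation that leaves out the staff time created by telemonitoring would miss part of that question, and the omission favours the intervention.

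**Working it through.** The plan gives no cost, alert rate, call length, wage or ICER, so there is no figure to reproduce. The check has three parts.

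**1. Activity against cost items**

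| Activity in the DM+TM arm | Counted under |
|---|---|
| Disease management system | Lump sum (both arms use the system) |
| Home devices | Lump sum |
| Clinic visit or admission following an alert | Structured form |
| GP, home care, nursing home | Patient questionnaire |
| Nurse reviews alert and telephones patient | No item named |

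**2. Direction**

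Let ΔC and ΔQ be the true differences in cost and QALYs (DM+TM minus DM), and let c > 0 be the uncounted alert-handling cost per DM+TM patient. The corresponding cost in the control arm is zero, because no alerts arise there.

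- Estimated incremental cost: ΔC − c.
- Estimated ICER: (ΔC − c)/ΔQ. If ΔQ > 0, this is too low by c/ΔQ.
- Net monetary benefit at willingness-to-pay λ: λΔQ − ΔC. The estimate is λΔQ − ΔC + c, too high by c at every λ and whatever the sign of ΔQ. The acceptability curve moves towards telemonitoring.

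**3. Size, under assumptions only**

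c = alerts per patient × (minutes per alert ÷ 60) × hourly cost. The only inputs from the plan are the 9-month horizon and the 130 patients in the DM+TM arm. The rest is assumed: 5 to 30 alerts per patient over 9 months, 10 to 20 minutes each, EUR 30 to 50 per hour.

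- Low: 5 × 10/60 × 30 = EUR 25 per patient; × 130 = EUR 3,250 for the arm.
- High: 30 × 20/60 × 50 = EUR 500 per patient; × 130 = EUR 65,000 for the arm.

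A wider set of assumptions (0.5 to 4 alerts per patient-month, 10 to 30 minutes, same hourly cost) gives:

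- Low: 0.5 × 9 × 10/60 × 30 = EUR 22.50 per patient.
- High: 4 × 9 × 30/60 × 50 = EUR 900 per patient.

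With EUR 25 to 500, the shift c/ΔQ depends strongly on the QALY gain, which is also assumed:

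| Assumed ΔQ | Understatement of ICER (EUR per QALY) |
|---|---|
| 0.01 | 2,500 to 50,000 |
| 0.02 | 1,250 to 25,000 |
| 0.05 | 500 to 10,000 |

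The direction follows from the plan's own description. The euro figures only illustrate scale.

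**The case against.** The strongest reply is that this is a condensed article. Neither the structured form nor the medical technology assessment questionnaire is shown, and the lump sum is not broken down. Installation, support or even staffing might sit inside it. This stands as a caution: a reader might infer that the trial will certainly not cost nurse time, and the text cannot prove that. But the article does more than stay silent. It states what the intervention costs are made up of, and it itemises resource use down to ward type and nursing home stays. The point is about that stated list.

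Four further readings are tempting and are not supported.

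- **A closed list under Randomisation and data collection.** That section says the data "comprise components of direct costs, i.e. scheduled and non-scheduled outpatient visits and hospital admissions". It cannot be exhaustive, because the costing section adds procedures, GP visits, home care and nursing home stays. It does not show that telephone contacts are excluded.
- **HF medication as part of the bias.** Medication is not listed either, but both arms use it and both receive up-titration advice. The direction of any resulting bias is unknown.
- **Replaced clinic visits booked as savings.** The Background says only that telemonitoring in general can be used to up-titrate at a distance. The arm descriptions specify no replacement of visits; the number of clinic visits is an outcome.
- **Nurse telephone time as negligible in control.** Alert handling is absent there, but control patients are counselled and may call the clinic. Those calls are uncosted too, so the net bias over all nurse calls could be smaller than c.

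Reach is also limited. The Statistical analyses section makes its cost-per-life-year analysis conditional on a mortality reduction, whereas the Cost-effectiveness section states the cost per QALY without condition. Whichever analysis is reported, the same costs enter it.

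**Conclusion.** The concern holds in this form: HF-nurse time for alert handling and the required call is part of the DM+TM intervention, arises only there, and is not among the listed costs. Followed as written, the plan understates incremental cost and favours telemonitoring in net monetary benefit and on the acceptability curve; the ICER is too low if the QALY difference is positive.

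This rests on reading the list as it stands, with no staff time inside the lump sum. A reader might infer a large distortion from the upper ends of the ranges. The documents do not support that: every input to the euro amounts is assumed apart from the 9 months and the 130 patients, and no device or admission cost is given against which to judge materiality. At the low end the effect may be trivial. It should be corrected because it has a known direction, bears on a stated secondary aim and is inexpensive to repair.

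**What to change.** - Add to the structured resource-use form the number and duration of HF-nurse telephone contacts in **both** arms, marking in the DM+TM arm those triggered by an alert. Cost them with the Dutch unit costs already planned.
- For patients already followed (recruitment began in December 2009), apply a timed sample of alerts to the alert counts in the disease management system, where these can be retrieved. The article says measurements reach that system but not that alerts are logged and exportable, so confirm this first.
- State whether the lump sum includes installation, support or nurse labour, so that nothing is omitted or counted twice. If it already covers alert handling, one sentence saying so settles the point.

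The cost is a few fields on an existing form, a little nurse logging, a data export if available, and possibly a less favourable ICER. Randomisation, the primary endpoint and the sample size are untouched.
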